### Economic evaluation

We will perform an economic analysis to investigate the cost-effectiveness of HPP compared to PT. The economic analysis can be performed from an insurer’s perspective, healthcare system perspective, and societal perspective; we have selected a societal perspective [38]. We will perform a cost-utility analysis including medical costs and non-medical costs, and costs associated with disease-related loss of production. For the final analysis results, we will present the incremental cost-effectiveness ratio (ICER) using the major economic assessment index of costs per quality-adjusted life year (QALY) gained [39]. ICER is an index that indicates the additional costs required per unit increase in effect, compared to an alternative. In addition, we will separately present the total effect (efficacy) and total costs of each treatment. For effect units, we will use QALY, which will be calculated using the quality of life derived by EQ-5D-5 L and using the area under the curve method with receiver operating characteristic (ROC) curves. For cost units we will convert all costs to 2019 South Korean Won (KRW), and apply 5% discount in accordance with the economic analysis guidelines of the Health Insurance Review and Assessment Service [40]. The treatment costs incurred by the clinical trial will be calculated by combining the treatment frequency and the unit costs; the unit costs will be calculated using the health insurance costs and the centre’s costs data. The analysis period is set to the entire clinical trial period (6 months), including the follow-up period. If estimates for the subsequent period are required, we will perform secondary analyses, such as extrapolating the costs and effects through a regression model or performing decision modelling analysis. In the baseline analysis, we will use representative values (mean, etc.) for the parameters used in the trial. To examine the uncertainty of the parameters used in the model, we will perform a sensitivity analysis; specifically, we will perform a probabilistic sensitivity analysis in which we estimate the prior distribution of the parameters, randomly extract the parameter values from these distributions, and use these results to perform a cost-effectiveness analysis.

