## Abbreviations

AAOP: American Academy of Orofacial Pain
AE: Adverse event
ANCOVA: Analysis of covariance
CRF: Case report form
CRP: C-reactive protein
EQ-5D-5 L: EuroQol-5 dimensions 5 levels
EQ-VAS: EuroQol Visual Analogue Scale
hCG: Human chorionic gonadotropin
HIRA: Health Insurance Review and Assessment Service
HP: Hominis placenta
HPP: Hominis placental pharmacopuncture
ICER: Incremental cost-effectiveness ratio
ICF: Informed consent form
iCReaT: Internet-based clinical research and trial
IRB: Institutional review board
ITT: Intention-to-treat
JFLS: Jaw Functional Limitation Scale
K-BDI: Korean version of Beck’s Depression Index
KHIDI: Korea Health Industry Development Institute
LOCF: Last observation carried forward
MI: Multiple imputation
NRS: Numeric Rating Scale
NSAIDs: Non-steroidal anti-inflammatory drugs
PA: Pharmaco-acupuncture
PGIC: Patient global impression of change
PP: Per protocol
PT: Physical therapy
QALY: Quality-adjusted life year
RCT: Randomised control trial
RDC/TMD: Research diagnostic criteria for temporomandibular disorders
RM ANOVA: Repeated measures analysis of variance
ROC: Receiver operating characteristic
ROM: Range of motion
SD: Standard deviation
SF-12: 12-Item Short-Form Health Survey
SOP: Standard operating procedure
SSRI: Selective serotonin reuptake inhibitor
TENS: Transcutaneous electrical nerve stimulation
TMD: Temporomandibular disorder
TMJ: Temporomandibular joint
VAS: Visual Analogue Scale
WHO-UMC: World Health Organization-Uppsala Monitoring Centre

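### The economic evaluation names the wrong curve for QALYs: a ROC curve cannot give utility multiplied by time, so the stated method for the ICER denominator cannot be carried out as written

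*Protocol article*

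**What the plan says.** The Economic evaluation section of the protocol article plans a cost-utility analysis from a societal perspective. Its final result is an incremental cost-effectiveness ratio, expressed as "costs per quality-adjusted life year (QALY) gained". On the effect side it states: "For effect units, we will use QALY, which will be calculated using the quality of life derived by EQ-5D-5 L", and then gives the method as "using the area under the curve method with receiver operating characteristic (ROC) curves".

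The Abbreviations section expands the term in the same way: "ROC: Receiver operating characteristic".

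On the horizon the section says: "The analysis period is set to the entire clinical trial period (6 months), including the follow-up period". Anything longer is conditional: "If estimates for the subsequent period are required, we will perform secondary analyses".

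Table 1 schedules the EQ-5D-5L in the week 1 column (visits 2 and 3, where visit 2 is also the baseline and allocation visit) and at weeks 4, 6, 9, 13 and 25.

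**The concern.** Two different quantities are called the area under the curve. In health economics it is the area under a participant's utility plotted against time, in units of quality-adjusted years. In diagnostic research it is the area under a plot of sensitivity against 1 − specificity, a probability of correct ranking between two classes. The plan spells out the second where only the first can produce a QALY.

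Economics is one of the three aims in the Background (efficacy, safety, economics), and the incremental QALY is the denominator of the economic result. The probabilistic sensitivity analysis in the same section depends on the same quantity. A prespecified method should be executable as it stands. Here the analyst must depart from the text and decide what was meant. The Blinding section says the data analyst is not blinded to group, so that decision is better fixed in writing beforehand.

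**Working it through.** The economic section states no QALY or ICER figure, so there is nothing of the plan's own to reproduce. The check has three parts: whether the stated method can be carried out, whether the intended one can, and on what scale.

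**1. Can a ROC area be formed, and would it be a QALY?**
- A ROC curve needs a binary reference state and a score that classifies it. The article plans no diagnostic test, no responder classification for this purpose and no binary state to predict.
- If one were formed, its area would lie between 0 and 1, with 0.5 meaning no discrimination. It would carry no unit of time. A QALY is utility × years. No rescaling turns one into the other.

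**2. Can the utility-time area be computed from the planned data?**

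Inputs, from Table 1: assessment times 0, 4, 6, 9, 13 and 25 weeks. The first mark stands under week 1. I take it as time 0 because visit 2 is both the baseline visit and part of week 1.

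Formula, trapezoidal rule with time in years:

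QALY = Σ (U_i + U_{i+1})/2 × (t_{i+1} − t_i)/52

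The weight of each assessment is half the sum of its adjacent intervals, divided by 52:

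| Assessment | Weeks of weight | Weight in years |
|---|---|---|
| Baseline | 4/2 = 2 | 0.0385 |
| Week 4 | (4+2)/2 = 3 | 0.0577 |
| Week 6 | (2+3)/2 = 2.5 | 0.0481 |
| Week 9 | (3+4)/2 = 3.5 | 0.0673 |
| Week 13 | (4+12)/2 = 8 | 0.1538 |
| Week 25 | 12/2 = 6 | 0.1154 |
| Sum | 25 | 0.481 |

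The data collection already planned is therefore sufficient.

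**3. The scale of the correct quantity**
- Maximum, with utility 1 throughout: 25/52 = 0.48 QALY.
- A difference of 0.05 in utility held for the whole period: 0.05 × 0.481 = 0.024 QALY.
- Illustration with assumed utilities (not from the documents): one arm at 0.75, 0.80, 0.84, 0.85, 0.85, 0.85 gives 20.875/52 = 0.4014. The other at 0.75, 0.78, 0.80, 0.81, 0.81, 0.81 gives 20.015/52 = 0.3849. The difference is 0.0165 QALY.

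**The case against.** The strongest defence is that this is a slip of wording that would do no harm. The same sentence correctly names the effect unit, the instrument and the area-under-the-curve method. The repeated EQ-5D-5L assessments to week 25 are what a utility-time area needs. With no classifier and no binary state in the trial, nobody could run a ROC analysis by following the text, so the likely outcome is that the error is noticed and the ordinary QALY calculation is done. The abbreviation entry only expands a term used in the text and is not evidence of a second, deliberate choice. All of this stands, and it limits the consequence. It does not make the sentence right: the wrong curve is positively stated, and nothing elsewhere in the article corrects it.

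A reader might go further and infer that the trial will report a meaningless cost per QALY. The article does not support that, because the stated method cannot be executed literally and the intended one is recognisable.

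A reader might also infer a second error from the discounting sentence, "For cost units we will convert all costs to 2019 South Korean Won (KRW), and apply 5% discount", set beside a 6-month analysis period: that costs alone are discounted and the ratio is thereby biased. That does not stand as an error, for four reasons:
- The article never says QALYs are left undiscounted. That reading rests on silence in a condensed article.
- The rate is taken from a national guideline that is not available here, so its treatment of effects and short horizons is unknown.
- The rate has a use in the optional extrapolation, which covers both costs and effects.
- The size is small. At 5% a year, 1 − 1.05^(−25/52) = 2.3% for a cost falling at week 25, 1 − 1.05^(−0.5) = 2.4% at six months, and about 1.2% if costs accrue evenly.

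At most, a clarifying clause on where the rate applies would help.

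**Conclusion.** The point holds. The QALY method is wrong as written, because a ROC area measures discrimination and cannot supply the denominator of the ICER. It is most likely a confusion of two meanings of AUC, and it is repaired without new data. The correct quantity is bounded by 0.48 QALY per participant, and plausible differences between arms are of the order of hundredths of a QALY (0.0165 to 0.024 in the two assumed examples).

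The correction should be made before the economic analysis is done, but it is not critical to the trial as a whole. The primary VAS comparison, the other efficacy outcomes, safety and the sample size are unaffected.

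The conclusion that the ROC wording is wrong needs no numerical assumption. The figures rest on the first EQ-5D-5L being taken as time 0, on nominal visit weeks and on a maximum utility of 1.

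**What to change.** In the Economic evaluation section, delete the reference to ROC curves and state instead: QALYs are the area under each participant's EQ-5D-5L utility-time curve by the trapezoidal rule, using the baseline assessment (visit 2, marked under week 1 in Table 1) and weeks 4, 6, 9, 13 and 25, with time in years. Remove ROC from the abbreviation list.

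Optional: say that the between-group QALY difference will be adjusted for baseline utility. This would match the baseline-adjusted ANCOVA already planned in the Statistical analysis section, but it is detail that may be left to the analysis plan.

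Cost: one sentence and one deleted abbreviation. No change to visits, data collection or sample size.

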### Data monitoring and safety monitoring

Monitoring will be performed by the monitoring coordinator at the coordinating centre. During monitoring, CRFs will be compared with evidentiary documentation, and participants’ safety data will be reviewed to verify the completeness of safety and research data. The monitoring will be conducted once every 2 months at two sites. The Trial Steering Group will meet to review conduct throughout the trial period once every 2 months. The Data Monitoring Committee was not organised as no severe AE regarding HPP or PT previously reported are expected to occur. The interim analysis will not be done in this study.

### Stopping rules

The principal investigator will decide the termination of the study; at any time during the trial period, if a participant is exposed to clear, unexpected risk or unacceptable risk, or if at least 25% of all participants experience severe AEs thought to be related to JHG002, the trial can be terminated. Severe AEs that might justify terminating the trial include local infection and severe progressive neurological deficits [41, 42].

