### Randomisation and allocation concealment

An independent statistics expert will use nQuery Advisior 7.0 (or SAS 9.0 [SAS Institute Inc., Cary, NC, USA] or SPSS 21.0 [IBM Corp., Armonk, NY, USA]) to allocate participants into each group by block randomisation in a 1:1 ratio (41 persons/group). The results of random allocation will be sealed, such that they cannot be seen from outside, and sent to each centre, where they will be managed in a double-locked container. Before treatment, a random envelope will be opened in front of the enrolled participant, the random allocation numbers assigned to each group will be recorded in an electronic chart, and no changes will be allowed after allocation. Participant enrolment at each centre will proceed by competitive enrolment.

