#### Treatment group: HPP group

After registration, the HPP group will receive two sessions/week of HPP for 5 weeks. For HPP, we will use JHG002, prepared at the Jaseng Namyangju Herbal Dispensary. The total treatment duration, frequency, one-time dose, and site of injection for HPP were selected with reference to previous studies [11, 15–17]. A trained doctor of Korean Medicine with at least 2 years’ clinical experience will administer JHG002 pharmacopuncture with a disposable syringe (0.5 ml) directly into the designated sites, using a standardised method. The injection sites were selected based on a textbook of acupuncture and moxibustion [17], and previous studies (Additional file 2) [18, 19]. The procedure will be performed bilaterally, irrespective of the location of pain, and at each session, 0.1 ml of JHG002 will be injected per acupoint at a total of eight locations. The dose will be adjusted in the range 0.05–0.1 ml per acupoint depending on the patient’s response (i.e. pain or discomfort).

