#### Control group: PT group (TENS)

The control group will receive two sessions/week of TENS for 5 weeks as a form of PT. We will use a high-frequency, low-intensity stimulus of 50–100 Hz and up to 15 mA, so that the patients feel a current but do not feel pain. At each treatment visit, a physiotherapist will administer the treatment to the bilateral TMJ for 15 minutes. Both centres will use the same TENS device—a BioTron-DX (D.M.C, Osan, South Korea).

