**Interventions**											
Treatment in JHG002 (experimental group)			← 2 times/week →								
Treatment in TENS (active control group)			← 2 times/week →								

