##### Adverse events (AEs)

All AEs will be investigated at each visit and recorded in the CRF; AEs do not need to show a clear causal relationship with the relevant treatment. Serious AEs will also be recorded [34]. Since the patient’s group may be revealed during AE assessment, this will be recorded by a subinvestigator in a separate CRF. All AEs will be classified according to the three-grade classification of Spilker et al. [35]^,^ into Mild (1): not impairing the participant’s normal daily life (or function), causing minimal discomfort, and readily endured; Moderate (2): causing discomfort that interferes significantly with the participant’s normal daily life (or function); or Severe (3): making normal daily life (or function) impossible. The causal relationship of AEs with the procedure will be classified according to the World Health Organization-Uppsala Monitoring Centre (WHO-UMC) causality scale, [34] as (1) definitely related, (2) probably related, (3) possibly related, (4) probably not related, (5) definitely not related, or (6) unknown.

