### Statistical analysis

As an RCT of chronic TMD patients, this study will compare the difference within and between groups for data on efficacy, safety, and economics. The main analysis will be the ITT analysis, and a PP analysis will also be performed. The demographic results, such as sex, age, occupation, and disease history, and the treatment expectancy will be assessed by group; continuous variables will be presented as the mean ± standard deviation (SD) and categorical variables will be presented as n (%). Differences will be tested using chi-square tests and independent *t* tests. Efficacy outcomes are the changes in continuous outcomes (VAS, NRS, K-BDI, JFLS, EQ5D-5 L, SF-12) at each time point relative to baseline. The primary outcome is the change in VAS from baseline to the primary end point (week 6) in each group. For safety outcomes, we will compare the incidence of AEs between groups; after graphing all the reported ARs in participants who have received treatment at least once, we will calculate the proportion of patients who have experienced AEs in each group, and compare these using chi-square tests and Fisher’s exact test. To compare the HPP and usual care groups, for continuous variables, we will perform an ANCOVA adjusted for the baseline outcome. For categorical variables, we will use chi-square tests of Fisher’s exact test, and to analyse within-group differences between time points, we will use paired *t* tests. Additionally, we will perform an ANCOVA adjusted for baseline outcomes and covariant factors that show a statistically significant difference between the treatment groups at baseline, and we will perform a repeated measures analysis of variance (RM ANOVA) to test differences in the changes across each visit. We will perform subgroup analyses according to RDC/TMD diagnosis (Group Ia, Ib), mouth opening, and K-BDI score. Missing values will be handled in a blinded state, mainly using multiple imputation (MI), last observation carried forward (LOCF) will additionally be used, and sensitivity analyses will be performed. All statistical analysis will be performed using SAS version 9.4 statistical package (SAS Institute, Cary, NC, USA), and statistical significance will be defined as *p* < 0.05.

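### The 25% stopping clause counts JHG002-related severe events over both arms, so it takes 21 of the 41 exposed patients (51%) to reach it

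*Protocol article*

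**What the plan says.** The Stopping rules section of the protocol article leaves termination to the principal investigator and gives two grounds. One is non-numeric: clear, unexpected or unacceptable risk to a participant. The other is numeric: "if at least 25% of all participants experience severe AEs thought to be related to JHG002". Either ground permits termination; neither requires it.

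Exposure to JHG002 is set out under Interventions. For the treatment group: "After registration, the HPP group will receive two sessions/week of HPP for 5 weeks. For HPP, we will use JHG002". For the control group: "The control group will receive two sessions/week of TENS for 5 weeks as a form of PT". Table 1 likewise lists JHG002 for the experimental group only. Participants are allocated "by block randomisation in a 1:1 ratio (41 persons/group"), 82 in total.

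The Adverse events section defines the top grade as "Severe (3): making normal daily life (or function) impossible". I read the stopping clause's use of severe as that grade.

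Under Data monitoring and safety monitoring there is no independent committee: "The Data Monitoring Committee was not organised as no severe AE regarding HPP or PT previously reported are expected to occur". The same section rules out an interim analysis.

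**The concern.** The numerator and the denominator of the numeric clause refer to different populations. Under the protocol, an event attributed to JHG002 can arise only in a patient given JHG002, which means the HPP group. The 25% is nevertheless taken over everyone, including the TENS patients. With equal arms this doubles the effective limit among those exposed.

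A reader of the clause, whether an ethics committee member or the investigator applying it, would take it to mean that one severe reaction in every four patients is the point at which the trial comes into question. In fact the clause is reached at about one in two of the patients who were injected. No other part of the article narrows the phrase to the HPP group. The planned safety analysis does use an exposed, per-arm denominator: "in participants who have received treatment at least once, we will calculate the proportion of patients who have experienced AEs in each group". That sentence concerns final reporting, so it does not contradict the stopping clause, but it shows the kind of denominator the protocol uses elsewhere.

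**Working it through.** **Inputs.** Total 82, 41 per arm, 1:1 (Randomisation and allocation concealment; Sample size). Threshold 25%, denominator all participants (Stopping rules). JHG002 assigned to the HPP arm only (Interventions; Table 1). The protocol gives no rate of JHG002-related severe events and no schedule for checking the clause, so the rates and check times below are assumptions.

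**The plan's own total.** A two-sample t test with d = 0.65, two-sided α = 0.05 and 80% power needs 39 per group (power 0.809), 78 in all. The ANCOVA factor gives (1 − 0.4²) × 78 = 65.52, stated as 65. Then 65 / 0.8 = 81.25, rounded up to 82. The stated 82 is reproduced.

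**Counts at full enrolment.**
- As written: 0.25 × 82 = 20.5, so 21 patients; 21/41 = 51.2% of the HPP arm.
- Exposed denominator: 0.25 × 41 = 10.25, so 11 patients; 11/41 = 26.8%.

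**Counts during accrual.** If all participants means those enrolled so far, and the arms are balanced, n HPP patients go with 2n in total. The written limit is 0.25 × 2n = 0.5n, against 0.25n for the exposed denominator, each rounded up.

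| HPP patients | Needed as written | Needed, exposed denominator |
|---|---|---|
| 10 | 5 | 3 |
| 20 | 10 | 5 |
| 30 | 15 | 8 |
| 41 | 21 | 11 |

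If instead the denominator is fixed at 82, the count is 21 throughout, so the clause cannot be met until at least 21 HPP patients have been treated.

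**Chance of reaching the limit, full enrolment only.** Binomial with n = 41: P(X ≥ 21) as written, P(X ≥ 11) with the exposed denominator.

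| Assumed true rate | As written | Exposed denominator |
|---|---|---|
| 5% | <0.01% | <0.01% |
| 10% | <0.01% | 0.2% |
| 25% | 0.03% | 45% |
| 40% | 9.7% | 97% |

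**Chance of reaching the limit at any check.** Exact calculation, arms assumed balanced at each check. Each cell gives as written / exposed denominator.

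| Assumed true rate | Checks at 10, 20, 30, 41 HPP patients | Check after every HPP patient from the 10th |
|---|---|---|
| 5% | 0.01% / 1.3% | 0.01% / 2.2% |
| 10% | 0.2% / 9.1% | 0.2% / 13.5% |
| 25% | 8.3% / 72% | 9.8% / 81% |
| 40% | 45% / 99% | 51% / 99.5% |

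The doubling of the count follows from the denominator alone. The probabilities show what it means only under the assumed rates.

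**The case against.** The strongest reply is that this clause controls nothing by itself. The principal investigator decides, the wording is permissive, and the unacceptable-risk clause would be met by any plausible cluster of related severe events well before 11 patients, let alone 21. Other safeguards exist. A participant can be withdrawn for a severe event (Dropout criteria). Adverse events are recorded and graded for causality at each visit, and laboratory tests are repeated at week 6. Monitoring and steering-group meetings take place every two months. The Stopping rules section also names kinds of severe event that might justify termination without attaching a count. All of this is true, and it limits the consequence: the denominator blocks no termination. But none of these is a numeric limit for the trial as a whole, and none changes what the 25% clause says.

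A second reply is that the sharp contrasts need true rates of 25% to 40%, whereas the protocol expects no severe events. That also stands: at 5% or below, the two versions hardly differ at full enrolment. A stopping limit, however, is written for the case in which the expectation fails.

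Third, the text can be applied literally, and nothing proves the sponsor meant 25% of exposed patients. That is fair as to intent. It does not make a denominator that is half unexposed suitable for a drug-specific reaction.

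Finally, other treatments are unrestricted after week 6, so a control patient could receive HPP outside the protocol. Incidental use would not justify counting every control as exposed, and a denominator based on actual exposure deals with it.

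**Conclusion.** The concern holds. As written, the only numeric safety limit in the trial needs 21 of 41 HPP patients (51.2%) to have a JHG002-related severe event, against 11 of 41 (26.8%) if the 25% is taken over those exposed. The doubling also applies during accrual if the denominator is current enrolment and the arms are balanced. The conclusion rests on JHG002 being given only in the HPP arm and on 1:1 allocation, both of which the protocol states; the trigger probabilities rest additionally on assumed event rates and check times. The practical consequence is limited by the unacceptable-risk clause and by the investigator's discretion. This is a badly set limit that should be corrected, not a failure of safety monitoring as a whole.

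**What to change.** In the Stopping rules section, change the denominator of the 25% clause from all participants to *participants who have received at least one JHG002 session*. Keep the 25%, the grade-3 meaning of severe, the freedom to act at any time, the unacceptable-risk clause and the permissive wording. At full enrolment, with all 41 HPP patients treated, the limit becomes 11.

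The change is a one-phrase amendment with no new visits or data. Its cost is that the limit is reached by chance more often. At an assumed true rate of 10% this is about 0.2% if checked only at full enrolment, about 9% over four checks and about 13.5% if checked after every patient from the 10th; as written the figures are below 0.01%, 0.2% and 0.2%. If the count runs from the first patient, one event among the first four HPP patients reaches the revised limit (as written, one among the first two), and at a 10% rate the overall chance is about 40% against 20%. Since reaching the limit permits termination without forcing it, and the investigator may already act on a single participant, this cost is acceptable.
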